### Randomization

After informed consent is signed, randomization into intervention or active control arms will be performed with a 1:1 allocation ratio. Balanced treatment assignments will be achieved using permuted block randomization, stratified by:

1) Abscess drainage (yes/no);

2) *K. pneumoniae* resistant to first-line agents (ceftriaxone or ciprofloxacin) (yes/no);

3) Study site.

The block length is determined by the study statistician and will not be made known to the clinical investigators or site personnel. All randomization will go through SCRI. Randomization will be done via direct web randomization. Authorized study center personnel will randomize the patient via a password protected internet website. The randomization system will then determine the treatment arm and provide the subject number to be used for the patient. The site monitor/clinical research associate (CRA) will be informed immediately in the event that the web randomization is not successful. Back-up randomization opaque envelopes (and related procedures) will also be prepared and provided to the site in case of internet failure.

Study arm allocation will not be blinded.

**Assessments**	**Pre-enrolment (routine care)**	**Screening**	**Once between day 0 and day 7**	**Day 2–3, rpt every 2-3d until negative**	**Any point in study period if temp ≥38°C and any other secondary infection suspected**	**Daily**	**Every 7 days (+/- 3d)**	**Day 28 (+/- 3d)**	**Day 42 (+/- 3d) **** *(if oral continued)* **	**Day 56 (+/- 3d) **** *(if oral continued)* **	**Day 70 (+/- 3d) **** *(if oral continued)* **	**Day 84 (+/- 7d)**
Informed consent		X										
Randomisation		X										
Demographics		X										
Past medical history^1^		X										
Antibiotic history		X^2^					X^3^	X^3^	X^3^	X^3^	X^3^	X^3^
Symptom assessment^4^		X					X	X	X	X	X	X
Temperature		X				X^5^	X^6^	X	X	X	X	X
Physical examination^7^		X					X	X	X	X	X	X
Screen metastatic complications^8^		X					X	X	X	X	X	X
Adverse event monitoring							X	X	X	X	X	X
Adherence check							X	X	X	X	X	X
Ophthalmology assessment			X									
FBC		X^9^					X	X	X	X	X	X
RP1		X^9^					X	X	X	X	X	X
LFT		X^9^					X	X	X	X	X	X
CRP		X^9^					X	X	X	X	X	X
Procalcitonin		X^9^					X	X	X	X	X	X
Urine pregnancy test		X^9^										
G6PD		X^10^										
Blood cultures	+/-	X^11^		X	X							
Chest X-ray		X^11^										
Abdominal CT or US	X^12^							X^13^		X^14^		X^15^
Abscess drainage^16^	+/-											
Abscess fluid culture^16^	+/-											
Study drug						X						
Subject diary of healthcare expenses						X						
Quality of Life Survey		X						X				X

^1^Full medical history including comorbidities, current medications, drug allergies, presenting and current symptoms. ^2^Document all antibiotics taken during this treatment episode up until enrollment. ^3^Include study drug and any additional antibiotics given. ^4^Standardized checklist. ^5^Self recorded daily temperature recording at home post discharge until Day 28 or until meeting criteria for clinical response. ^6^Self recorded weekly temperature recording at home after meeting criteria for clinical response, with weekly reminder call from the study team. ^7^Measurement of blood pressure, heart rate, and cardiovascular, respiratory and abdominal examination. ^8^Screen consists of standardized checklist of symptoms and signs, which if present trigger relevant investigations. ^9^If not already done in previous 48 hours. ^10^Only in patients whose *K. pneumoniae* tests resistant to ciprofloxacin, and those with contraindications to ciprofloxacin. ^11^If not already done in previous seven days. ^12^Scans must be within the preceding seven days. ^13^Day 28 scan to be performed within three days prior to the Day 28 visit. ^14^Day 56 scan to be performed within three days prior to the Day 56 visit, only in those patients failing to meet criteria for clinical response at day 42. ^15^Day 84 scan to be performed within three days prior to the Day 84 visit, only in those patients failing to meet criteria for clinical response at day 70. ^16^At any point during the current treatment episode.

Patients will be reviewed every seven days whilst inpatient. Assessment will consist of a standardized clinical assessment consisting of temperature, blood pressure, heart rate, symptom assessment and clinical examination. Blood tests (FBC, RP1, LFT, CRP, procalcitonin) will be performed a minimum of once every seven days while in hospital. In addition, temperature will be measured daily for all participants until Day 28 or meeting criteria for clinical response, whichever is longest. While inpatient or in OPAT this is part of routine clinical care; and for patients on the intervention arm (oral antibiotics), patients will be given thermometers to use daily after hospital discharge. Repeat blood cultures will be performed at day two to three post randomization on all patients with a positive blood culture at/prior to enrollment. If this remains positive it will be repeated every two to three days until negative. This is to ensure clearance of bacteremia.

Following discharge, participants in both arms of the study will be reviewed weekly in the OPAT clinic with a standardized clinical assessment consisting of temperature, blood pressure, heart rate, symptom assessment, clinical examination and blood tests (FBC, RP1, LFT, CRP, procalcitonin) as well as an adherence check for both study arms (pill count for subjects on oral; OPAT nurse documentation and infusion bottle count for subjects on IV). Within the three days preceding the Week 4 visit, all study participants will undergo follow-up abdominal imaging (CT or US) as per current standard of care in these cases. If participants do not meet criteria for clinical response at Week 4, there will be a further Week 6 appointment at the end of the two week extension of oral antibiotics. Patients not satisfying the criteria for clinical response after Week 6 will receive two weekly extensions of oral antibiotics and two weekly visits, until they meet criteria for response. Patients not meeting criteria for clinical response by the Week 6 visit will have a repeat abdominal scan (CT or US) arranged for within three days prior to the Week 8 visit. Patients not meeting criteria for clinical response by the Week 10 visit will have a repeat abdominal scan (CT or US) arranged for within three days prior to the Week 12 visit. There is no upper limit to the duration of antibiotics, but subjects will not be followed up beyond Week 12 within the study. Patients not meeting criteria for clinical response by the Week 12 visit will have failed to meet the primary endpoint of clinical cure, and will thereafter revert to routine clinical care.

All participants will return to a follow-up assessment at Week 12. This assessment will follow the same format as the preceding visits, with standardized clinical assessment consisting of temperature, blood pressure, heart rate, symptom assessment, clinical examination and blood tests (FBC, CRP, and procalcitonin).

The following direct and indirect costs over the whole study period will be collected from administrative sources where possible, and by self-report otherwise. Patients will be asked to maintain a diary of health care-related utilization and expenditures as well as to retain all related receipts and bills collected during the period of the study.

1) Inpatient treatment (hospital cost and billing systems for procedures, diagnostics and pharmaceuticals, verified against patient hospital bill): inpatient stay cost, diagnostics, supplies, antibiotics required for study treatment, other medications outside study treatment.

2) Outpatient care (patient diary, verified against copies of bills and receipts where possible): consultations at outpatient clinic, polyclinic, general practitioner, emergency department visit, ambulance service, care at community-based facilities.

3) Outpatient medication and supplies (patient diary, verified against copies of bills and receipts where possible): prescriptions; over the counter medication; other equipment and supplies.

4) Caregiver time (patient diary): hours spent by caregiver and identity of caregiver: whether professional or working/nonworking relative.

5) Patient time (patient diary): hours spent in treatment and additional days of work absenteeism.

6) Transport costs (patient diary, verified against copies of bills and receipts where possible): hours spent in transit to facilities for follow-up/other care, cost of transportation.

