### Study endpoints

The primary endpoint is 'clinical cure’, determined at Week 12 post-randomization, and defined as CRP < 20 mg/l, plus absence of documented fever ≥ 38°C in the preceding week, plus most recent abdominal imaging showing that the maximal diameter of the abscess has reduced.

The main secondary endpoint is 'clinical response’, determined at Week 4 post-randomization, and defined as CRP < 20 mg/l, plus absence of documented fever ≥ 38°C in the preceding week, plus most recent abdominal imaging showing that the maximal diameter of the abscess has reduced. Other secondary endpoints (assessed at Week 12) are:

• all-cause mortality at any point between randomization and Week 12;

• unplanned readmission for any cause at any point between hospital discharge and Week 12;

• unplanned need for drainage after enrollment at any point between randomization and Week 12 (the screening visit will document any plans for elective drainage);

• metastatic complications occurring at any point between randomization and Week 12;

• new *K. pneumoniae* bacteremia occurring at any point between the first negative blood culture, and Week 12, with the same strain of *K. pneumoniae* as the original blood culture or abscess fluid culture determined by antibiotic susceptibility pattern);

• length of hospital stay (from the date of randomization to the end of inpatient stay, censored at Week 12);

• length of time the subject requires medical leave following hospital discharge (censored at Week 12);

• subject quality of life as defined by the WHOQOL-BREF assessed at Week 4 and Week 12 post-randomization;

• overall cost of each treatment strategy from the payer and total societal perspective for the course of the study until the final 12 Week follow-up;

• level of adherence during the entire study period, assessed at 12 weeks. Subject deemed to be compliant if 80% or more of prescribed antibiotics have been taken.

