Ceftriaxone and ertapenem will be given IV using either peripheral cannula or a peripherally inserted central catheter (PICC) once daily. Administration may be done as inpatient, in OPAT or a step-down facility by healthcare staff, or at home by patients or their caregivers after training by OPAT staff (all these methods are currently in routine clinical use for patients on prolonged IV antibiotics). Ciprofloxacin and trimethoprim/sulfamethoxazole will be administered orally in tablets from each site’s pharmacy either as inpatient or at home. Patients on ciprofloxacin may not take tizanidine or theophylline or concomitant drugs that can result in prolongation of the QT interval (for example, class IA or class III antiarrhythmics).

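### Thermometers are named only for the oral arm, so documented fever, a component of the primary endpoint, may be ascertained unequally by arm, most clearly in the week before Week 12

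*Protocol article*

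**What the plan says.** Under Study visits and procedures, the governing rule covers both arms: "temperature will be measured daily for all participants until Day 28 or meeting criteria for clinical response, whichever is longest". The text then gives two ways of meeting it. The first is ordinary care: "While inpatient or in OPAT this is part of routine clinical care". The second is a device for one arm: "for patients on the intervention arm (oral antibiotics), patients will be given thermometers to use daily after hospital discharge".

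The Table 1 footnotes describe home recording with no limit to one arm. Footnote 5 reads "Self recorded daily temperature recording at home post discharge until Day 28 or until meeting criteria for clinical response". Footnote 6 reads "Self recorded weekly temperature recording at home after meeting criteria for clinical response, with weekly reminder call from the study team".

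Under Study endpoints, clinical cure at Week 12 and clinical response at Week 4 both include "absence of documented fever ≥ 38°C in the preceding week", together with a CRP criterion and an imaging criterion. The Randomization section states that allocation is not blinded.

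Two further facts decide how far ordinary care covers the control arm. Under Study intervention, IV treatment may be given by staff or "or at home by patients or their caregivers after training by OPAT staff". Under Study design, control IV treatment runs to the Week 4 assessment. Patients without a clinical response at that point move to oral antibiotics with a visit every two weeks.

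**The concern.** The fever component depends on what is recorded, so a fever that nobody measures counts towards success. If one arm has a thermometer at home and the other depends on contact with staff, the chance of recording the same fever can differ by arm for reasons unrelated to treatment.

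This affects the primary endpoint and the main secondary endpoint. Temperatures also feed the intention-to-treat imputation of dropouts, which uses the last two recorded values. A temperature of 38°C or more is also part of the Table 1 trigger for repeat blood cultures, which bears on detecting new bacteremia, a secondary endpoint. With only 5% of control patients expected to fail, a small difference in ascertainment is not negligible.

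**Working it through.** **1. What is owed in each period, and by what means**

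| Period after discharge | Home or daily reading owed (both arms) | Oral arm: means | Control arm: means | Clinic reading (both arms) |
|---|---|---|---|---|
| To Week 4 | Daily | Thermometer | OPAT routine care; not assured daily if IV is given at home by patient or caregiver | Weekly |
| After Week 4, no response yet | Daily under the text; less clear under footnote 5 | Thermometer | None named; IV has ended | Every two weeks |
| After response | Weekly, with reminder call (footnote 6) | Thermometer | None named | Week 12 visit |

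Up to Week 4 the stated frequency is the same in both arms. The method differs (self-recorded against staff), and there is a gap in frequency only for control patients treated at home. After Week 4 the staff route no longer applies to control patients. At Week 12 a clinic reading covers one day of the seven-day window in both arms. The rest depends on home recording.

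**2. How many control patients could owe daily readings after Week 4**

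The preliminary OPAT cohort had a 73% response at four weeks on the same definitions. If that carried over, 1 − 0.73 = 27% would be non-responders, and 0.27 × 76 ≈ 20 control patients before attrition. The protocol itself says the cohort was selected, so this is only an order of magnitude.

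**3. An internal mismatch**

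Footnote 5 lets daily recording end at Day 28 or at response. The text says whichever is longest. The two differ for patients who have not responded by Day 28, who are the patients in the second row of the table.

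**4. The plan's own sample size**

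Inputs from Determination of sample size: control cure 95%, margin 0.12, one-sided alpha 0.025, power 0.8, z-test with continuity correction, 64 per arm, 15% attrition. The oral-arm rate is not stated; 95% is assumed.

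- Test: declare non-inferiority if (p_oral − p_control + 0.12 − 1/n) exceeds 1.96 × √[(p_control(1 − p_control) + p_oral(1 − p_oral))/n], using observed proportions.
- Exact binomial enumeration gives power 0.807 at n = 64 and 0.753 at n = 63. The normal approximation with the same correction gives 0.773 at n = 64.
- Attrition: 64/0.85 = 75.3, rounded up to 76 per arm, 152 in total. The plan's figures reproduce.

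**5. Illustration of sensitivity**

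This is an assumption, since the documents give no fever rate. Let true cure be 95% in both arms, and let unequal ascertainment add an excess e of recorded fever failures to the oral arm only. Exact power of the test in step 4 at 64 per arm is then:

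| e (percentage points) | Power |
|---|---|
| 0 | 0.807 |
| 1 | 0.700 |
| 2 | 0.586 |
| 3 | 0.473 |
| 5 | 0.282 |

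The lower rows are severe. Total expected control failure from all causes is 5%, so a 3-point excess equals 3/5 = 60% of it.

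**The case against.** The best defence is that the thermometers exist to equalise monitoring. The rule is daily temperature for all participants. Control patients on IV have regular contact with staff; oral patients do not, so they get a device. The footnotes then set one schedule for both arms. The text never says that control patients go without a thermometer, and supply details may sit in the full protocol, which is not shown. This stands for most control patients up to Week 4. It does not explain how control patients record at home once IV has stopped, nor how those treated at home before then are read daily. The arm-specific sentence is an instruction in the article, not an omission from it.

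A reader might go further and infer three things that the documents do not support.

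- *Control patients pass the fever component by default.* They do not. Both arms have clinic temperatures, including at Week 12, and cure also needs the CRP and imaging criteria, which active infection may well fail. After response the oral arm also owes only one home reading a week, so its own detection would be far from complete.
- *The bias can be sized.* Supposing that 3% or 5% of patients have fever as their only failed criterion, with all such fevers found in the oral arm and half in control, gives 0.5 × 3% = 1.5 or 0.5 × 5% = 2.5 points against the 12-point margin. Neither the fever rate nor the detection rate has a source. A fever-only rate of 3% to 5% would be 60% to 100% of all expected failures.
- *The imbalance would produce a false claim of non-inferiority.* More fever found in the oral arm lowers its observed cure rate and works against the claim. The reverse is possible, for example if oral patients skip self-readings while staff measure control patients, but it is not the likelier direction.

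**Conclusion.** The point holds in a limited form. Followed as written, the article leaves fever open to unequal ascertainment by arm in an open-label trial whose primary endpoint depends on documented fever. The gap is narrow up to Week 4, where it concerns control patients given IV at home. It is clearest after Week 4, including the week before the Week 12 assessment. Clinic readings in both arms reduce it.

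Its size is unknown, because no fever rate is given. The power figures show only that one or two spurious points would matter at 64 per arm, assuming 95% true cure in both arms and an excess confined to the oral arm. The more likely consequence is lost power rather than a false non-inferiority claim, but the direction is not certain. The sample size is not in dispute. The change is worth making because it is cheap and protects a component of the primary endpoint.

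**What to change.** State that every patient in both arms receives the same thermometer and recording card at discharge and follows the same recording schedule through Day 84. State that fever is scored from the same sources in both arms: the home record plus the clinic reading. Reconcile footnote 5 with the text on when daily recording ends, so that one rule applies to patients who have not responded by Day 28.

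The cost is about 76 more thermometers (152/2), one protocol sentence and the footnote alignment. The sample size does not change. Self-recording stays unblinded, so the change equalises the means and schedule of recording but cannot guarantee equal diligence.

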### Study endpoints

The primary endpoint is 'clinical cure’, determined at Week 12 post-randomization, and defined as CRP < 20 mg/l, plus absence of documented fever ≥ 38°C in the preceding week, plus most recent abdominal imaging showing that the maximal diameter of the abscess has reduced.

The main secondary endpoint is 'clinical response’, determined at Week 4 post-randomization, and defined as CRP < 20 mg/l, plus absence of documented fever ≥ 38°C in the preceding week, plus most recent abdominal imaging showing that the maximal diameter of the abscess has reduced. Other secondary endpoints (assessed at Week 12) are:

• all-cause mortality at any point between randomization and Week 12;

• unplanned readmission for any cause at any point between hospital discharge and Week 12;

• unplanned need for drainage after enrollment at any point between randomization and Week 12 (the screening visit will document any plans for elective drainage);

• metastatic complications occurring at any point between randomization and Week 12;

• new *K. pneumoniae* bacteremia occurring at any point between the first negative blood culture, and Week 12, with the same strain of *K. pneumoniae* as the original blood culture or abscess fluid culture determined by antibiotic susceptibility pattern);

• length of hospital stay (from the date of randomization to the end of inpatient stay, censored at Week 12);

• length of time the subject requires medical leave following hospital discharge (censored at Week 12);

• subject quality of life as defined by the WHOQOL-BREF assessed at Week 4 and Week 12 post-randomization;

• overall cost of each treatment strategy from the payer and total societal perspective for the course of the study until the final 12 Week follow-up;

• level of adherence during the entire study period, assessed at 12 weeks. Subject deemed to be compliant if 80% or more of prescribed antibiotics have been taken.

Safety endpoints include: need to stop study drug due to toxicity; toxicity as defined by Common Terminology Criteria for Adverse Events version 4.03 [17]; all adverse events (occurrence of adverse events up to 12 weeks post randomization or 30 days post last study dose if later than 12 week visit); serious adverse events (occurrence of serious adverse events at any time during the study period, whether or not they are thought to be related to the study drugs); need to escalate antibiotics due to worsening infection or secondary infection at any point between randomization and Week 12; vascular catheter complications at any point between randomization and Week 12.

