### Aims

Our study’s primary aim is to compare the efficacy of four weeks of IV antibiotics to early step-down to oral antibiotics in patients with KLA. Our results would help inform local and international practice guidelines regarding the optimal antibiotic management of KLA. A finding of non-inferiority in terms of clinical efficacy may translate to the wider adoption of a more cost-effective strategy that reduces hospital length of stay and improves patient-centered outcomes and satisfaction.

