### Objectives

The primary objective is to compare the rate of clinical cure after four weeks of IV antibiotics to early step-down to oral antibiotics in patients with *Klebsiella pneumoniae* liver abscess, with clinical cure determined at Week 12 post randomization, and defined as CRP < 20 mg/l, plus absence of documented fever ≥ 38°C in the preceding seven days, plus most recent abdominal imaging showing that the maximal diameter of the abscess has reduced. The main secondary objective is to compare the rate of clinical response between the two study arms, with clinical response determined at Week 4 post-randomization, and defined as per clinical cure. Other secondary objectives are to compare the rate of the following during the study period, between the two study arms (assessed at 12 weeks): all cause mortality; unplanned readmission for any cause; unplanned need for drainage; metastatic complications; recrudescent or breakthrough *K. pneumoniae* bacteremia; need to escalate antibiotics due to worsening infection or secondary infection; vascular catheter complications. Additionally, to compare the length of hospital stay (from the date of randomization to the end of inpatient stay), length of time the subject requires medical leave following hospital discharge (censored at 12 weeks), total cost, subject quality of life (QoL), and adherence to study drug between the two study arms.

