### Study design

This study is a multi-center randomized open-label active comparator-controlled non-inferiority trial. Subjects fulfilling the inclusion/exclusion criteria are randomized to one of two arms: intervention arm; or active control arm, as shown in Figure 1. Participants randomized to the active control arm will receive IV ceftriaxone 2 grams daily (or ertapenem 1 gram daily if resistant) to complete a total of four weeks of IV antibiotics until the assessment at Week 4 post randomization. Patients can be discharged to OPAT at any point post randomization if clinically well, at the discretion of the treating physician/ID team. Patients discharged to step-down care will be followed up in OPAT clinic at the same weekly intervals as patients discharged to home. Patients will be assessed at Week 4 for clinical response. If they do not meet criteria for clinical response (as defined in the section on endpoints) then they will receive a further two weeks of oral ciprofloxacin 750 mg twice daily (or trimethoprim/sulfamethoxazole 5 mg/kg twice daily if resistant) and then re-reviewed (see below).

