The primary analysis will be conducted on both the per-protocol population and intention to treat population. The study will claim non-inferiority based on the results of the analysis on both the per protocol and ITT population. For the ITT, drop outs will be imputed as clinical cure if they meet all of the following criteria: last two CRPs show a downward trend or are < 20; last two recorded temperature measurements < 38°C; contact established via phone call at day 84 (+/- 7 days) and patient reports they are symptom free. If the criteria are not met then the case will be imputed as a clinical failure. The exact method will be used to test the hypothesis of non-inferiority for the pre-specified non-inferiority margin of 12%. A two-sided 95% confidence interval (CI) for the treatment difference will be calculated and compared with the equivalence margin (12%). If this 95% CI for the treatment difference excludes the non-inferiority margin (12%) then there is evidence of non-inferiority.

The Fisher’s exact test will be used to compare 12 week mortality between the two treatment arms and the associated exact 95% confidence interval will be calculated using the Clopper and Pearson method. Additionally we will calculate the time from baseline to death for each treatment group using the Kaplan-Meier product-limit method, censoring at the 12 week assessment, those that withdraw or are lost to follow-up during the study period will be censored at the point of last follow-up. Fisher’s exact test and the Clopper and Pearson CI will be calculated for all other binary endpoints between the two treatment arms. The Mann–Whitney *U-*test will be used to compare the duration of inpatient stay and the length of time the subject requires medical leave following discharge between the two treatment arms.

Quality of life data will be measured using the WHOQOL-BREF. The two overall items (overall perception of quality of life and overall perception of health) and the four domain scores (physical, psychological, social and environmental) will be examined. The Student’s *t*-test will be used to compare the change from baseline at both 4 weeks and 12 weeks for each of these scores between treatment arms, as well as the change between 4 weeks and 12 weeks. In further exploratory analysis we will fit a mixed model to examine the effect of time and treatment on each of the four domain scores.

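### Length of hospital stay ends with the inpatient stay, so readmission days before Week 12 are left out and equal total inpatient days can look like a saving

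*Protocol article*

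**What the plan says.** Under Study endpoints, the article lists "length of hospital stay (from the date of randomization to the end of inpatient stay, censored at Week 12". The Objectives section gives the same interval, "length of hospital stay (from the date of randomization to the end of inpatient stay", but without the Week 12 cap. Under Statistical analysis, the Mann-Whitney test "will be used to compare the duration of inpatient stay" between arms.

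Two neighbouring endpoints in the same list cover related events: "unplanned readmission for any cause at any point between hospital discharge and Week 12" and "all-cause mortality at any point between randomization and Week 12". Both are binary and fall under Fisher's exact test.

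The Study design section treats step-down care as a place to which a patient is discharged: "Patients discharged to step-down care will be followed up in OPAT clinic at the same weekly intervals as patients discharged to home". That sentence stands in the description of the IV arm. The description of the oral arm mentions discharge home only.

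The Aims section links a finding of non-inferiority to wider adoption of a "more cost-effective strategy that reduces hospital length of stay". The abstract's Discussion says the same.

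**The concern.** The endpoint is one interval with one end. Readmission is defined as something that happens after hospital discharge, so the inpatient stay has already ended when a readmission begins, and its days fall outside the measure. If the end were instead taken as the last discharge before Week 12, days at home before a readmission would count as hospital days. Neither reading gives the number of days spent in hospital.

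This matters more here than in a blinded trial. Allocation is open, and in both arms discharge is at the discretion of the treating team, so the length of the index stay can respond directly to knowledge of the arm. Early discharge followed by readmission is also a plausible way for an oral strategy to fail. What is at stake is one of the benefits that the article attaches to non-inferiority, a shorter hospital stay.

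**Working it through.** **Inputs.** The article states no expected length of stay, standard deviation, power or readmission rate for this endpoint, so there is no figure of its own to reproduce. From the document: 152 patients, hence 152 / 2 = 76 per arm (Determination of sample size), and a mean hospital stay of 15 days in the outpatient-IV cohort (Preliminary studies). That 15 days is borrowed here as an assumed length of readmission; it is not a readmission figure. All index stays and readmission rates below are assumptions.

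**Formula.** Mean total inpatient days = mean index stay + readmission rate × mean readmission length. The days that the rule misses in the between-arm difference are therefore

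(readmission rate, oral − readmission rate, IV) × mean readmission length.

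**Main illustration.** Index stay 6.5 (oral) v 8 (IV) days; readmission 15% v 5%, 15 days each.
- Rule as written: 6.5 − 8 = −1.5 days.
- Total days, oral: 6.5 + 0.15 × 15 = 8.75.
- Total days, IV: 8 + 0.05 × 15 = 8.75. Difference 0.0.

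In simulation (gamma-distributed index stays, shape 1.5, two-sided 0.05), the Mann-Whitney test on index stay was significant in about 30% of trials, against about 7% on total days. A repeat run with every readmission fixed at 15 days gave 28% and 6%.

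**Range over other assumed inputs**

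| Index stay, oral v IV | Readmission, oral v IV | Days each | Index difference | Total difference | Significant, index | Significant, total |
|---|---|---|---|---|---|---|
| 6 v 7 | 15% v 5% | 10 | −1.0 | 0.0 | 23% | 5% |
| 6 v 8 | 20% v 5% | 14 | −2.0 | +0.1 | 63% | 6% |

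These two rows used gamma shape 2. With equal readmission rates the formula gives no distortion. If the IV arm were readmitted more often, the sign would reverse.

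**Does the readmission endpoint reveal it?** At 76 per arm, Fisher's exact test has about 45% power to detect 15% v 5%. More often than not, a trial in the main illustration would report no significant readmission difference, and that endpoint carries no days in any case.

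**Step-down days.** Assume that 20% of the IV arm spends 14 days in step-down care: 0.20 × 14 = 2.8 days left out of the IV arm. With index stays of 6 v 8 days, the oral advantage is −2.0 as written and −2.0 − 2.8 = −4.8 once those days count. This omission works against showing a saving.

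**Deaths in hospital.** With equal index stays of 8 days and deaths of 5% v 0% or 10% v 0%, scoring a death as a completed stay moves the mean by about 0.2 or 0.4 days. Mann-Whitney rejection is then 6% or 8%, against a nominal 5%.

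**The case against.** A stay that ends at discharge is a conventional measure, and the article surrounds it with companions: unplanned readmission, mortality, and overall cost to Week 12, which covers inpatient stay and community-facility care. The economic claim therefore does not rest on length of stay. This stands, and it limits the reach of the point. It does not repair the endpoint, because a yes/no readmission rate cannot be converted into days.

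The illustrations are also built so that totals cancel, and they rest on assumed rates. That is fair: they show what the rule can do, not what this trial will show. A more dramatic case, 5 v 8 days with readmission 25% v 5%, makes the false saving significant in about 90% of trials. But Fisher's test would detect that readmission gap with 93% power, so the excess would almost always be reported beside the shorter stay. That case should not carry the argument.

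A reader might go further and infer that every omission favours the oral arm. The document does not support that. Step-down care is mentioned only for the IV arm, so leaving it out hides a saving. Death has no stated rule within this endpoint, but its effect is small, its direction depends on which arm has the deaths, and a condensed article may leave that detail to the full protocol or analysis plan. Nor does the text say that the interval ends at the first discharge. That is the natural reading, given how readmission is defined, but the article does not use the word.

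**Conclusion.** The point holds for readmission days. The article fixes the start, stop, cap and test of the endpoint, and the stop leaves out later inpatient days. With a readmission gap of 10 percentage points and 10 to 15 days per readmission, the rule can show 1.0 to 1.5 days saved when none is. Such a result is significant in roughly a quarter to a third of trials of this size. These figures depend wholly on assumed stays and readmission rates, and on the oral arm being the one readmitted more often. The consequence is limited to the length-of-stay comparison and the benefit drawn from it; the primary endpoint and the cost analysis are unaffected. The change is worth making because it is cheap and gives the quantity that the Aims section needs.

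**What to change.** Define length of hospital stay as total inpatient days from randomization to Day 84, including every readmission. Keep the planned Mann-Whitney comparison and add the difference in means, since the mean is what translates into bed-days. Retain the index stay as a descriptive line. Add the Week 12 cap to the Objectives section so that the two definitions agree. Report days in step-down facilities separately by arm.

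There is no need to score deaths as 84 days. That would turn the measure into a composite partly driven by mortality, which is already an endpoint.

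The cost is about one sentence in the endpoint definition. Readmissions and inpatient billing are already followed to Week 12. The case report form should record admission and discharge dates for each readmission, and dates for step-down stays, because the article describes facility care only as a cost item. The downside is small: unrelated readmissions add some noise.
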